## Abstract

**Background:**

Childhood apraxia of speech (CAS) is a pediatric motor-based speech sound disorder that requires a specialized approach to intervention. The extant literature on the treatment of CAS commonly recommends intensive treatment using a motor-based approach, with some of the best evidence supporting the use of Dynamic Temporal and Tactile Cueing (DTTC). To date, a rigorous and systematic comparison of high and low dose frequency (i.e., frequency of therapy sessions) has not been undertaken for DTTC, resulting in a lack of evidence to guide decisions about the optimal treatment schedule for this intervention. The current study aims to fill this gap in knowledge by comparing treatment outcomes when dose frequency is varied.

**Methods:**

A randomized controlled trial will be conducted to examine the efficacy of low versus high dose frequency on DTTC treatment outcomes in children with CAS. A target of 60 children, 2;6–7;11 years of age, will be recruited to participate in this study. Treatment will be provided in the community setting by speech-language pathologists who have completed specialized training administering DTTC in a research reliable manner. True randomization with concealed allocation will be used to assign children to either the low or high dose frequency group. Treatment will be administered in 1-h sessions either 4 times per week over a 6-week period (high dose) or 2 times per week over a 12-week period (low dose). To measure treatment gains, probe data will be collected before treatment, during treatment, and 1 day, 1 week, 4 weeks, and 12 weeks post-treatment. Probe data will consist of customized treated words and a standard set of untreated words to assess generalization of treatment gains. The primary outcome variable will be whole word accuracy, encompassing segmental, phonotactic, and suprasegmental accuracy.

**Discussion:**

This will be the first randomized controlled trial to evaluate dose frequency for DTTC treatment in children with CAS.

**Trial registration:**

ClinicalTrials.gov identifier NCT05675306, January 6, 2023.

## Background

Childhood apraxia of speech (CAS) is a pediatric motor speech disorder that affects the planning and programming of speech movements [1, 2] and is estimated to occur in 1 per 1000 children [3]. Children with CAS typically have severe speech deficits that result in poor speech intelligibility, which will not resolve without appropriate targeted intervention (ASHA, [4]). There is a general consensus in the field that intense and frequent motor-based treatment is required to help remediate CAS [5–7]; however, empirical evidence specifying the optimal frequency of treatment sessions is lacking. While it seems intuitive to predict that more frequent sessions would result in greater treatment gains than less frequent sessions–even when cumulative dosage is kept constant–findings from previous research are conflicting [8]. The objective of the current work is to therefore examine the effect of dose frequency (i.e., frequency of therapy sessions) on treatment outcomes in Dynamic Temporal and Tactile Cueing (DTTC; [9]), one of the few evidence-based motor-based treatment approaches for CAS [6, 7].

### Dynamic Temporal and Tactile Cueing treatment (DTTC)

DTTC is a dynamic, motor-based treatment approach designed for children with severe CAS. This approach is based on Integral Stimulation [10–14]. In which the clinician instructs the child to “listen to me, watch me, and do what I do” and systematically supports the speech motor system to facilitate system-wide change in speech output [9]. In contrast to more traditional intervention approaches for speech sound disorders, the target of DTTC is speech movement gestures practiced in the context of real-word/phrase targets to optimize functional communication and be maximally motivating to the child. Within DTTC, the speech-language pathologist (SLP) engages the child in structured practice along a temporal hierarchy, where targets are first practiced at a slow rate and then progress to a regular rate as accuracy increases. Practice occurs across four levels: Simultaneous Production, Direct Imitation, Delayed Imitation and Spontaneous Production. At each level, the clinician dynamically varies the amount and type of supportive cueing provided, with the end goal being the child’s independent and accurate movement gestures within word- or phrase-level productions. Multisensory cueing (i.e., visual, tactile, gestural, verbal) is provided to support accurate speech production and cues are added/faded depending on the individual needs of the child. As the child becomes more independent in achieving accurate movement gestures, models and cues are faded to facilitate the child’s learning, retention, and generalization to untreated similar exemplars. Previous efficacy research on integral stimulation treatment, including DTTC, has generally used single-case experimental design studies and demonstrated moderate-to-large treatment and generalization effects for the majority of participants in the small samples studied [8, 10, 12, 13, 15–17]. Larger studies that control for or covary individual factors such as attention, severity, and resilience are needed to better understand what is driving varying responses to treatment for children in this heterogeneous population.

### Treatment intensity

Treatment intensity is a critical factor for optimizing speech motor learning [18]. There are a number of ways in which intensity can be operationalized [19] including the number of practice trials or teaching episodes per session (i.e., 'dose'; [10, 11]), number of total practice trials/teaching episodes over a period of time (i.e., ‘cumulative intervention intensity’; [20]), and frequency of treatment sessions (i.e., ‘dose frequency’; [21–23]). Investigations of treatment intensity in children with CAS reveal improved treatment outcomes when participants produce a higher number of trials per session [10] and when a greater number of practice trials are produced for a smaller stimulus set [11]. For instance, in a production frequency study of two children with CAS receiving integral stimulation treatment, Edeal and Gildersleeve-Neumann [10] reported better treatment outcomes for targets that were practiced 100 + times during each session compared to those practiced 30–40 times.

The extant literature on dose frequency in CAS is equivocal. Namasivayam, Pukonen [20] examined the impact of session frequency in 37 children with CAS within a play-based motor speech protocol therapy completed by community clinicians. Children received motor-based intervention once (low intensity) or twice per week (higher intensity), 60 min per session, for 10 weeks in community clinics. Findings revealed better treatment outcomes for the higher intensity, twice per week, condition in which children had received 20 sessions as compared to 10 sessions in the lower intensity group. Notably, no speech intelligibility gains were detected for either group, possibly suggesting that neither condition was sufficiently intense to promote these important gains. Leonhartsberger, Huber [8] also investigated the effect of session frequency on integral stimulation treatment outcomes in four German-speaking children with CAS when cumulative dosage was kept constant across conditions. Children were engaged in high intensity treatment (two 30-min treatment sessions daily for 2 weeks) followed by a period of low intensity intervention (one 60-min session each week for 10 weeks). Participants received a total of 10 h per treatment phase. Performance was compared between the high- and low-intensity conditions and revealed similar outcomes in each condition. Given that treatment order was not counter-balanced across children, it is unclear whether similar outcomes for both conditions could be attributed to a “jump-start” effect of the high-intensity condition. Thomas, McCabe [21] investigated outcomes of Rapid Syllable Transition (ReST) treatment provided two times per week over a 12-week period (*n* = 4). When compared to previous research that tested the efficacy of ReST administered 4 times per week over a 3-week period [22], analyses revealed similar initial treatment gains for both treatment intensities. However, children who received the more intense treatment schedule typically showed a rising profile even after treatment was completed whereas those who underwent the less frequent sessions showed no ongoing improvement once treatment ended.

Contrasting findings for treatment intensity have also been reported for children with non-CAS speech sound disorders [24]. High intensity intervention (3x/week over 8 weeks) yielded improved gains as compared to low intensity intervention (1x/week over 24 weeks) for a phonological intervention administered with the same cumulative dosage across groups [24]. In contrast to Thomas, McCabe [21], similar gains at maintenance were reported for both the high- and low- intensity groups. Taken together, these findings indicate a range for the effect of intensity on treatment outcomes within the CAS literature and other populations. Given that intensive treatment–specifically high frequency of clinical sessions per week–is widely recommended for children with CAS, it is critical to investigate how differing levels of intensity impact speech performance to provide evidence for clinical decision-making. Large scale, rigorous study of dose frequency in children with CAS is essential to determine whether high or low dose frequency is superior in effecting learning and generalization, or if schedule can be decided based on family and clinician preference and availability [25].

Previous work that examined treatment intensity in children with CAS, for various treatments, is limited by a variety of factors including small sample size [10, 11, 21], a lack of randomized control trials (RCTs) with true randomization (e.g., [20]), and under-specified protocols that make assessment, group assignment, and treatment difficult to replicate (cf. [26]). Consequently, it can be difficult to glean which treatment schedules will promote optimal learning and generalization outcomes for children with CAS.

### Current study

The proposed study aims to address these limitations by conducting an RCT to compare the effects of high and low dose frequency treatment schedules for a large sample of children with CAS undergoing DTTC speech treatment. To assess differences in treatment outcomes when dose frequency is varied, speech production accuracy will be tracked using whole word accuracy. The primary outcome measure will be whole word accuracy quantified using a multi-factor whole word accuracy measure, the Multilevel word Accuracy Composite Scale (MACS; [27]), which systematically accounts for segmental and prosodic accuracy, word shape maintenance, and smoothness and fluency of movement transitions. Secondary outcome measures will include phoneme accuracy (Percent Phonemes Correct; [28]), speech intelligibility (Intelligibility in Context Scale; [29]), and functional communication (Functional Outcomes on Communication Under Six; [30]). This RCT is expected to yield easily interpretable evidence to better understand the effect of dose frequency on treatment outcomes. We hypothesize that similar treatment and generalization gains will be detected for both the high and low dose frequency groups when cumulative dosage is constant (i.e., after 24 sessions have been completed). However, we predict that the high dose frequency group will demonstrate superior outcomes following 6 weeks of treatment when the high dose frequency group has completed 24 sessions and the low dose frequency group has completed 12 sessions. Based on our previous research [21, 22] and the extant literature, we also predict that the high dose frequency group will demonstrate superior maintenance of treatment and generalization gains compared to the low dose frequency group. Thus, while both conditions are predicted to yield positive treatment gains, we hypothesize the high dose frequency group to display these gains in a shorter timeframe and with greater maintenance and generalization as compared to the low dose frequency group.

## Methods and design

The proposed work is a multisite Phase III parallel-group RCT that aims to investigate the outcomes of DTTC in children with CAS (ages 2;6 to 7;11) and determine whether dose frequency impacts response to treatment. Participants will be randomly assigned to receive DTTC treatment at a low dose frequency (2x/week over 12 weeks) or high dose frequency (4x/week over 6 weeks). Group assignment will be performed using concealed randomization. All assessments and treatment will be provided by community SLPs throughout North America. All of the clinicians working on this study will undergo a rigorous application process, as well as extensive training including numerous applied activities. They will receive ongoing feedback from the investigators, who are SLPs with expertise in CAS, throughout the study to ensure high adherence to experimental protocols and fidelity to the operationalized assessment and treatment approaches.

### Ethical approval and consent to participate

This trial was registered on ClinicalTrials.gov, identifier NCT05675306, on January 6, 2023. Ethics approval for this study was obtained through the Marquette University Institutional Review Board (Protocol HR-4095). Informed consent to participate will be obtained from parents or caregivers on behalf of all participants. Assent will also be obtained from children who are 6 years of age and older.

### Targeted enrollment

We plan to enroll 60 children with CAS with potential to recruit an additional 6 children to account for a 10% rate attrition if needed. The power analysis for the treatment effect comparing the Lower Dose Frequency treatment group to the High Dose Frequency treatment group during the immediate-post testing period was done using a latent growth curve model [31, 32]. Specifically, the power analysis was conducted with respect to whole word accuracy, the primary outcome. Mplus [33] was used for power analysis with a sample size of 60 (30 per group). Mplus calculates power by simulating data given the design. In the simulation, the effect size is defined as change in the primary outcome between the low dose frequency group and the high dose frequency group divided by the square root of the model variance (a quantity similar to Cohen’s *d)*. At type one error of 5% (two tailed test) and a moderate treatment effect of 0.35, the power for estimating the treatment is 80%.

### Participants

This RCT is a multi-site study with up to 35 different community clinic treatment sites in the United States and Canada and 5 sites for data processing and analysis (Marquette University, Hofstra University, New York University, the University of Vermont, and the University of Sydney). Candidates for participation will be told about the study by their treating clinician using a script created by the research team. Alternatively, parents may respond to a flyer or postings on a website or social media account (e.g., Apraxia Kids). If the child’s parent/caregiver is interested in the study, they will complete the online screener to determine whether the child meets the minimum inclusionary criteria. The completed screeners will be reviewed by the research team. If a child meets screening criteria, the research team will contact the caregiver and describe the study and informed consent process in greater detail. If at that point the family would like to have their child participate, the research team will obtain a digital signature on the Informed Consent document using the HelloSign program; parental/caregiver informed consent to participate will be obtained for all participants. A digital signature will also be obtained on an assent document for children ages 6;0–7;11 (years;months). If additional support is needed to recruit our target of 60 participants, we will advertise through listservs, personal contacts, and flyers posted in public locations such as schools, pediatricians’ offices, and libraries. Participant enrollment will begin in January 2023.

Inclusionary criteria for child participants include (1) CAS diagnosis confirmed by research team as described below (e.g., [34–36]), (2) 2;6–7;11 years of age at treatment commencement; (3) English as the primary language; (4) no concomitant developmental disorders (including autism, global developmental delay, intellectual disability); (5) no diagnosis of severe or primary dysarthria as described below; (6) no palatal or structural orofacial anomalies as described below, (7) no uncorrected vision impairment (8) no hearing loss; (9) not receiving speech treatment elsewhere over the course of this study, although language, augmentative and alternative communication (AAC) treatment, or similar non-speech treatment, would be permitted (10) Receptive Language Index standard score greater than or equal to 70 on the Receptive-Expressive Emergent Language Test, 4^th^ edition (REEL-4; [37]) for children 2;6–2;11 years of age, the Clinical Evaluation of Language Fundamentals – Preschool 3^rd^ edition (CELF-P3; [38]) for children 3;0–5;11 years of age, or the Clinical Evaluation of Language Fundamentals – 5^th^ edition (CELF-5; [39]) for children 6;0–7;11 years of age, (11) Nonverbal Index standard score greater than or equal to 70 on the Developmental Assessment of Young Children-2^nd^ edition (DAYC-2; [40]) for children 2;6–5;11 years of age, the Reynolds Intellectual Assessment Scales– 2^nd^ edition, Remote (RIAS; [41]) for children 6;0–7;11 years old, and (12) evidence of communicative intent, attempts at verbal communication, focused attention to the clinician’s face, and demonstrated ability to imitate during the Dynamic Evaluation of Motor Speech Skill (DEMSS; [35]). All eligibility assessments will be administered by community speech-language pathologists and scored by the research team.

Participants will not be excluded from the proposed study on the basis of sex/gender or racial/ethnic group. Male and female children will be recruited, although we expect that males will enroll in higher numbers than females given that CAS occurs in 2–3 males per female [3].

### Assessment procedure

Consented participants will undergo a full diagnostic eligibility assessment and, if they qualify, will complete additional assessment tasks and be invited to undergo the treatment portion of the study. Parents/caregivers will complete a case history form about their child’s developmental, medical, and birth history, including brief information regarding their child’s siblings. If a child does not meet the inclusionary criteria after the eligibility assessment (e.g., due to deficits in language skills or hearing loss), they will be told that they do not meet criteria for participation in the treatment phase of the study. They will receive a $50 stipend for participating in the assessment.

The eligibility assessment protocol will include the Goldman Fristoe Test of Articulation-3rd edition (GFTA-3; [42]), a polysyllabic word test (Toddler Test of Polysyllables; [43]), an oral mechanism assessment, story retell of “Frog, where are you?” [44], and the DEMSS [35, 45]. If the child is unable to complete the story retell task, elicitation of a spontaneous speech sample will be attempted during play. Language will be assessed using the REEL-4 [37] for children under 3, the CELF-P3 [38] for children 3;0–5;11 years, or the CELF-5 [39] for children 6;0–7;11 years. The Intelligibility in Context Scale (ICS; [29], a 7-item parent survey, will be administered to assess communicative effectiveness. Resilience will be screened using the Child and Youth Resilience Measure (CYRM) – Revised ([46], Resilience Research Centre; [47]). Attention will be screened using the Conners Early Childhood Parent Survey [48] or the Conners-3 Parent Survey [49], depending on the child’s age. Nonverbal IQ will be assessed using the Developmental Assessment of Young Children (DAYC-2; [40]) in children 2;0–5;11 years of age or the Reynolds Intellectual Assessment Scales (RIAS; [41] in children 6;0–7;11 years of age. The Focus on the Outcomes of Communication in Children under Six (FOCUS-34; [30]) will be used to screen quality of life. Eligibility assessments will take place over the course of up to 3 1-h sessions, over 1–2 weeks.

#### Differential diagnosis of CAS

Differential diagnosis of CAS will be confirmed for each child by one member of the research team based on performance on the DEMSS, a dynamic speech assessment (e.g., [35]) and the presence of auditory-perceptual features consistent with CAS (e.g., [9, 34, 36]). Features associated with CAS and timing and coordination across speech subsystems will be observed on the following tasks: (1) dynamic speech assessment (i.e., DEMSS; [35]); (2) single word articulation testing (i.e., GFTA-3; [42]); (3) connected speech; (4) multisyllabic word productions (i.e., TPOT; [43]); (5) motor speech examination. An oral structural–functional examination will also be conducted to rule out any confounding craniofacial anomalies (e.g., submucosal cleft) or overt lower motor neuron dysarthria and to detect the presence of oral motor apraxia. The Profile of Childhood Apraxia of speech and Dysarthria (ProCAD; [34]) be used to identify articulatory and prosodic features that are discriminative of CAS and present in two or more speech contexts and to rule out the presence of features associated with dysarthria (motor execution issues) only. Performance across assessments will also be evaluated to rule out primary diagnosis of other speech sound disorders associated with an articulation or phonological impairment. Inter-rater reliability for differential diagnosis will be conducted on 10% of participants.

#### Group allocation

For participants who meet inclusionary criteria following the eligibility assessment, group allocation will be specified by the study statistician using a computer-generated random number list. The group assignments will be put into sequentially numbered, opaque, sealed envelopes with the specified group number indicated inside the envelope. This will help to conceal the randomization sequence until group assignments are made. The study statistician will generate confidential treatment assignments for participants 1 through 30 and participants will receive their group assignment in the order in which they are enrolled in the treatment phase. After 30 participants are enrolled, we will conduct preliminary group comparisons of participant demographics to determine the extent that the groups are balanced. If there are statistically significant differences between groups on potentially confounding demographic variables such as age, language ability, or speech severity, we will attempt to rebalance the groups for the subsequent 30 participants who are enrolled. Speech severity will be established through combined analysis of scores from dynamic motor speech skill assessment (DEMSS) and single word articulation testing (*GFTA-3*). In cases where a participant withdraws prior to the completion of the study, the next participant to enroll will be assigned to the same treatment condition to be the substitute. Participants and clinicians will be told which group each participant is assigned to by the research team after the informed consent document has been signed and eligibility has been determined by the eligibility assessments.

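### The substitute rule fixes the arm of the child who enrols after a withdrawal, contrary to the randomised and concealed allocation that the trial claims; the rebalancing step has a poor trigger and no stated mechanism

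*Protocol article*

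**What the plan says.** The Abstract (Methods) states: "True randomization with concealed allocation will be used to assign children to either the low or high dose frequency group". Methods and design repeats that assignment is randomised and concealed.

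The Group allocation section gives the mechanism: "group allocation will be specified by the study statistician using a computer-generated random number list", placed in numbered, opaque, sealed envelopes. It describes this list for half of the trial only: "The study statistician will generate confidential treatment assignments for participants 1 through 30".

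The same section then adds two departures:

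- **Substitutes.** After a withdrawal before study completion, "the next participant to enroll will be assigned to the same treatment condition to be the substitute".
- **Rebalancing.** After 30 children the groups are compared. "If there are statistically significant differences between groups on potentially confounding demographic variables such as age, language ability, or speech severity", then "we will attempt to rebalance the groups for the subsequent 30 participants who are enrolled". No test level, method, random element or concealment is given.

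On who knows what, Group allocation says: "Participants and clinicians will be told which group each participant is assigned to by the research team". The Participants section says: "The completed screeners will be reviewed by the research team", and has the same team obtain consent. Under Differential diagnosis of CAS, one member of that team confirms each diagnosis.

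**The concern.** Sealed envelopes protect only the assignments drawn from them. A substitute's arm does not come from an envelope. It follows from who has just withdrawn. The research team announces the arms and would be expected to learn of withdrawals, and it also decides who enters. Part of that decision is a perceptual diagnosis, with inter-rater reliability checked in 10% of participants. After a withdrawal, the people controlling entry can therefore know the next child's arm before that child is accepted. Concealment exists to rule this out.

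Two things are at stake. First, selection at entry becomes possible in a trial whose team predicts an advantage for high dose frequency at 6 weeks and at maintenance. Second, children who were never randomised stand in for randomised children who left. The Potential limitations section relies on randomisation to minimise clinician and site effects, and that protection does not extend to substitutes.

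The rebalancing step raises a lesser question: whether a baseline significance test at 30 children is a sound basis for changing how the other 30 are allocated.

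**Working it through.** **The plan's own figure.** Targeted enrollment gives 60 children, 30 per group, plus 6 for 10% attrition: 60 × 0.10 = 6 and 60 + 6 = 66. The figure is reproduced. The point disputes no stated number.

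**1. Share of assignments fixed by the substitute rule.** With w withdrawals, each replaced once, the share is w/(60 + w).

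| Withdrawals | Share fixed |
|---|---|
| 3 (assumed) | 3/63 = 4.8% |
| 6 (planned) | 6/66 = 9.1% |
| 12 (assumed) | 12/72 = 16.7% |

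The text sets no limit on substitutes, so 6 is not a maximum.

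**2. Possible shift in an arm's mean.** Suppose that all 6 substitutes fall in one arm and differ prognostically from randomised children by δ SD. Both are assumptions. The shift is 6δ/n, where n is that arm's size in the analysis:

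- all enrolled children: n = 30 + 6 = 36;
- completers only: n = 30.

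| δ (assumed) | n = 36 | n = 30 |
|---|---|---|
| 0.25 | 0.04 SD | 0.05 SD |
| 0.5 | 0.08 SD | 0.10 SD |
| 1.0 | 0.17 SD | 0.20 SD |

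In a plain comparison of two means with 30 per arm (standard error √(2/30) = 0.258 SD, normal approximation), biases of 0.05, 0.10 and 0.20 SD raise the two-sided 5% error to 5.4%, 6.7% and 12.1%. The planned growth model would give somewhat different figures.

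**3. Quality of the rebalancing trigger.** Assume 15 per arm at the check and a 5% test level (neither is stated for this check).

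- Power of a two-sample t-test to flag a true imbalance of 0.5 SD: about 26% (28% by normal approximation).
- Chance of at least one false trigger over the three variables named, if the tests are independent: 1 − 0.95³ = 14.3%. For five variables it is 1 − 0.95⁵ = 22.6%.

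The check would therefore miss about three in four imbalances of 0.5 SD, and would fire about one time in seven when randomisation had worked as intended.

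**The case against.** Several points on the other side are fair.

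- **Rebalancing.** A reader might infer that this step also assigns children non-randomly and predictably. The text does not support that. The step is conditional and its method is unstated; a stratified or minimised scheme with a random element, run by the statistician, would fit the wording. A condensed article may leave the mechanism to the full protocol. The weakness of the trigger stands, because the article does state the trigger.
- **Arm-related withdrawal.** A reader might infer that substitutes will collect in the high-frequency arm, since Potential limitations expects some families to find four visits a week burdensome. That passage concerns preference about group assignment. Families also receive a stipend for each session and agree all dates before baseline testing. No withdrawal pattern by arm is given, and the 12-week schedule could lose families too.
- **Bias against the design effect.** It is tempting to express the shift as a fraction of the planned effect of 0.35. That effect is scaled by the square root of the growth model's variance, which is not shown to equal the outcome SD used above.
- **Foreknowledge.** That the screening staff would know the next arm is a reasonable inference from shared roles, not a stated fact. Families and clinicians learn the assignment only after consent and eligibility.
- **Safeguards already planned.** The plan includes intention-to-treat and per-protocol analyses, a baseline comparison of completers with withdrawn children, covariates, and transcribers blinded to group and time point. These limit harm, but none makes a substitute's assignment random or concealed.

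Nothing in the article cancels the substitute rule.

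**Conclusion.** The concern holds for the substitute rule. It is explicitly deterministic, the team controlling entry can foresee its result, and it contradicts the article's claim about allocation. That conclusion needs no numerical assumption.

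Its scale is about 6 of 66 assignments (9%) at the planned attrition. The illustrative shift of 0.08 to 0.10 SD rests on two assumptions: all six substitutes in one arm, and a 0.5 SD prognostic difference. The documents give no evidence that either will happen. Apart from any substitutes among them, the first 30 children remain properly randomised and concealed.

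For rebalancing the conclusion is narrower. Allocation of the second 30 may turn on a weak significance test that is prone to false alarms, with no random or concealed mechanism described. It is a poor trigger and needs a stated mechanism. It is not shown to break randomisation.

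**What to change.** 1. Delete the substitute rule. Every child, replacements included, takes the next sealed envelope from a concealed list held by the statistician and extended beyond 60.
2. State that withdrawn children stay in their randomised arm in the intention-to-treat analysis already planned under Statistical analysis plan.
3. Remove the significance-triggered rebalancing. Rely on the covariate adjustment already described under Statistical analysis plan and Data cleaning and preparation, or pre-specify a scheme, run by the statistician, that keeps a random element and concealment.
4. Flag any child already assigned as a substitute, and run a sensitivity analysis without those children.

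The cost is a change of wording and a longer envelope list. No extra children or visits are needed, and the planned 66 stands. The number of assignments fixed by a withdrawal falls from about 6 to 0. The downside is that final arm sizes may differ slightly from 30:30.
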